### Randomisation

A computer-generated sequence of serial numbers for up to 1000 participants paired with a random series of allocation numbers (1 for usual care or 2 for the brief, structured intervention) is used to allocate the participants to either trial group. The allocation sequence is based on simple randomisation and is concealed to counsellors, clients and interviewers until the baseline interview is performed. The research coordinator prepares the sequential numbered, sealed envelopes containing a folded note of the group allocation. At the end of the baseline interview, interviewers open the sealed envelope according to the serial number sequence and disclose the allocation, i.e., assign clients to the trial condition.

#### Blindness

Because of the nature of the study, it is impossible to blind the counsellor and the participants concerning the content of the received intervention. However, neither the counsellor nor the participants are aware of the specific effect measures of the study. As the disclosure of the group allocation will take place after recruitment in the study and after the baseline interview, the knowledge of trial group allocation will not influence counsellors in their first contact with the clients. Further, it will not influence the interviewers and the participants at the moment of collecting the baseline information. Moreover, the outcome assessment at follow-up will be conducted by interviewers blinded to the participant’s allocation.

### Data collection

The assessment of clients’ characteristics and of the outcome is conducted using a structured questionnaire with closed-ended response alternatives administered via telephone interviews at baseline, 6-month and 12-month follow-up. The questionnaire includes demographics, the AUDIT scale, self-rated health, sick leave, depression or anxiety symptoms (M.I.N.I.) and help-seeking due to problematic alcohol use. Figure 2 displays the process of recruitment, allocation according to the SPIRIT guidelines.

**Fig. 2 Fig2:**
[figure not shown]
Standard Protocol Items: Recommendations for Interventional Trials (SPIRIT) schedule of enrolment, intervention and assessment, including information of staff members and task duration. *Usual care – tailored counselling mixed approach reactive and proactive calls as agreed. Starts from week 1 or when client wishes to contact the Swedish National Alcohol Helpline (SAH) and continues as needed

The baseline interview is conducted 5–15 working days after the first call. Follow-up interviews are collected 26 weeks (±2) and 52 weeks (±2) after the baseline interview.

A maximum of five call attempts are made to reach participants at each stage of the data collection, and text messages are additionally used as alerts or to schedule interviews. A research coordinator ensures that participants are followed-up within the appropriate time interval. Data of the process, compliance to the study protocol and adherence of the client will be gathered from the client records kept at the SAH. Available information includes: conduct of proactive and reactive calls as agreed, number of contacts during the study period, and length of each contact.

#### Training of interviewers

Interviewers are not involved in the counselling at the SAH. They receive information about the study and are provided with a quick reference guide containing expressions to use during the interview and a protocol to handle critical events, e.g., expressed suicidal thoughts. Interviewers are trained to assist during three sessions with experienced personnel before conducting any interview on their own.

#### Data security, quality and management

The same rules for data protection and confidentiality are applied for the computerised client record used in the trial as for clinical records in health care. The password-protected record is kept at the SAH, and is used in the everyday management. De-identified information from each participant’s SAH record (baseline AUDIT, duration and number of calls) and data from interviews will be merged into one database, available to investigators in the study team. All employees at the SAH, as well as the personnel in the study team who access personal information, sign a confidentiality agreement upon employment.

Steps involving data management, analysis and interpretation will be carried out by a study team independent both from the funders and from the SAH management. The study team consist of a project leader, a coordinator, a statistician and the interviewers collecting the data. Withdrawal from participation in the trial will instantly be documented in the SAH record and enable participants to contact the SAH for regular counselling. The study process and recruitment process will be discussed in monthly meetings including personnel from the study team and SAH.

Because of the size and nature of the trial, no interim analyses of the intervention’s effects are planned; moreover we do not expect adverse outcomes or significant results before the endpoint. However, loss to follow-up in the two trial conditions is closely monitored as an indication of unfavourable outcome in any group. For the above reasons, no formal data monitoring committee has been assigned.

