### Setting

The trial is carried out at the SAH, a telephone service with national coverage that provides free-of-charge counselling on two to three parallel lines, operating 33 h per week, on weekdays. Written information about the SAH is readily available in health care settings, at the Internet and in social media. The SAH is financed by the Public Health Agency of Sweden and Stockholm County Council (SCC) that also holds the operational responsibility of the service.

In 2015, the SAH received 1849 calls from individuals who were consuming hazardous or harmful amounts of alcohol. There were 640 clients who called for the first time, 58% of whom were men. For first-time callers, the mean age was 48 years for men and 46 years for women (available for *n* = 415), and the mean Alcohol Use Disorder Identification Test (AUDIT) score was 21.1 and 21.5 for men and women, respectively (available for *n* = 407).

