#### Procedures for missing data

Losses to follow-up will be first and foremost analysed in reference to differential selection. As a primary approach, all available participants will be analysed. As a second step, we will perform sensitivity analyses using ‘worst case scenario’ (loss to follow-up equalised to no change or change to a higher AUDIT category) as well as last observation carried forward (LOCF) in the long-term follow-up. As a third step we will analyse whether missing outcome information can represent cases of at least missing at random (MAR). In this latter case multiple imputation of missing variables data will be conducted, and the results compared with those of the available cases analysis.

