#### Information and informed consent

Information about the study is provided at different stages of the recruitment process. Oral information is provided at the initial call to the SAH, followed by the dispatch of written information in Swedish, by mail or e-mail, to interested clients within one week. Additionally, written information is available on the website (alkohollinjen.se/om-alkohollinjen/studier-pa-alkohollinjen/pagaende-studie/).

At the time of the telephone interview, the staff ascertains that clients have received and understood the information. At this point, informed consent is obtained orally and registered in the survey form.

All participants are informed that participation is voluntary and that they can choose to withdraw from the study at any point. The identity of the participants is not disclosed at any time and participants have the possibility to use an alias rather than their actual name during the contacts with both SAH and study staff. All participants are entitled to receive a summary of their registered personal information on a yearly basis.

Due to the inclusion and exclusion criteria and to the nature of the trial, we do not expect any harmful consequence of the counselling in either study arm.

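### Loss to follow-up is the named between-arm indication of unfavourable outcome, but it cannot register a client who worsens and still completes the interview, and no stated outcome counts worsening by arm

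*Protocol article*

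**What the plan says.** In the protocol article, under *Data security, quality and management*, the plan is that "no interim analyses of the intervention’s effects are planned; moreover we do not expect adverse outcomes or significant results before the endpoint". It then adds that "loss to follow-up in the two trial conditions is closely monitored as an indication of unfavourable outcome in any group", and closes with "For the above reasons, no formal data monitoring committee has been assigned". No threshold for a difference in loss, and no action following one, is given. In the same section, "The study process and recruitment process will be discussed in monthly meetings including personnel from the study team and SAH"; harms are not named as a topic. *Information and informed consent* states that "we do not expect any harmful consequence of the counselling in either study arm".

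Two other provisions bear on the point. *Training of interviewers* gives interviewers "a protocol to handle critical events, e.g., expressed suicidal thoughts". *Procedures for missing data* says "As a primary approach, all available participants will be analysed", followed by sensitivity analyses. One of these is a worst-case analysis that sets lost clients to no change or to a higher AUDIT category.

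*Primary outcome* and *Statistical analysis* define success as any downward move in AUDIT risk level, yes or no. *Secondary outcomes* counts clients who move from indicated depression or generalised anxiety disorder to none, sick-leave days cut by at least half, self-rated health that improves out of the two lowest answers, and any help-seeking for alcohol problems at other providers.

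**The concern.** The article picks one quantity to compare between arms as a sign that clients are doing badly, and that quantity measures whether they were reached, not how they are. Someone who is interviewed and has a higher AUDIT score, or newly meets the M.I.N.I. criteria for depression, is a retained client under this indicator.

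The indicator can also move without harm. The brief arm has no counsellor-initiated contact after its single proactive call, while usual care allows a varying number of calls. Willingness to be interviewed could therefore differ between arms for reasons unrelated to outcome.

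The *Discussion* says that superiority of the brief intervention would be a strong reason to move the service to the less labour-intensive model. A service making that decision needs to know whether more clients got worse under reduced contact, as well as whether more improved. The interviews collect what is needed, but the outcomes as coded would not show it.

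**Working it through.** **Inputs.** *Sample size*: 300 recruited, at least 250 analysed, 125 per arm. *Primary outcome*: top AUDIT band from 20 (men) and 18 (women), scale maximum 40. *Data collection*: interviews at 26 and 52 weeks, each ±2. The protocol gives no figure for harm monitoring, so there is none to reproduce. Its design figure of more than 90% power for 30% versus 50% at 125 per arm does reproduce (90.2%, two-sided 5%), but this point does not rest on it.

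**Step 1: what each kind of client contributes.**

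| Client at follow-up | Loss indicator | Primary outcome |
|---|---|---|
| Reached, lower risk level | retained | yes |
| Reached, same level | retained | no |
| Reached, worse | retained | no |
| Not reached | lost | not in the available-case analysis; no under worst case |

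The second and third rows are identical in both columns. Worsening among reached clients cannot be separated from no change by either measure. The worst-case analysis concerns only the fourth row. On a yes/no outcome it too scores worsening and no change alike.

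**Step 2: how much of the sample this covers.** Implied loss is (300 − 250)/300 = 16.7%, about 25 of 150 per arm. The remaining 250/300 = 83.3%, about 125 per arm, are reached.

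**Step 3: how far excess worsening moves the loss rate.** Let L be ordinary loss, h the excess proportion worsening in one arm, and m the loss among those extra clients. That arm's loss is L + h(m − L), so the between-arm difference is h(m − L). Take L = 16.7% and, as an assumption, h = 10 percentage points (15 of 150 clients):

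- m = 16.7%: 0.10 × (0.167 − 0.167) = 0. Fifteen more clients are worse and loss does not change.
- m = 50%: 0.10 × (0.50 − 0.167) = 3.3 points, 20.0% versus 16.7%, or 30 versus 25 clients lost.
- m = 100%: 0.10 × (1 − 0.167) = 8.3 points, 25.0% versus 16.7%, or 37.5 versus 25 expected.

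The indicator carries information only so far as worsened clients are lost more often than others. The documents give no value for m.

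**Step 4: other outcomes.** M.I.N.I., sick leave and self-rated health are each defined as improvement. Help-seeking elsewhere is not, but it can reflect either deterioration or constructive action.

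**Step 5: what a replacement must include.** A client in the top AUDIT band can rise from 20 (men) or 18 (women) up to 40 without changing category, so a count of upward shifts has a ceiling. In *Setting*, the mean first-time caller's "score was 21.1 and 21.5 for men and women, respectively", above both cut-offs. These are helpline callers in 2015 with a score available (n = 407), not randomised clients. They show only that the ceiling could affect many clients, and that the score itself is needed.

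**The case against.** The strongest reply is that this is a low-risk counselling trial with several safeguards. Severe dependence, severe mental illness and suicidal intention are excluded. Concomitant care is allowed, and brief-arm clients may call back and receive usual counselling. Interviewers have a procedure for critical events, and withdrawals are documented at once. The worst-case analysis does treat loss as unfavourable. The article is also a condensation: the interviewer procedure is not shown, and a full protocol or analysis plan may say more about harms. Regular by-arm outcome tables would come close to the interim look that the plan rules out.

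Much of this stands, and it blocks several stronger readings that a reader might reach:

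- *That loss is the only harm signal.* The critical-event procedure is another safeguard. It works client by client, however, and the article describes no count of events by arm.
- *That loss is confounded by contact intensity.* Follow-up is done by interviewers outside the counselling, blinded to allocation, with a five-attempt limit and no difference by arm stated. Only 'may differ' is supported.
- *That caller severity contradicts the no-harm expectation.* The AUDIT means precede exclusions and consent, and the expectation concerns the counselling, not baseline severity.
- *That a comparison of loss has a particular statistical power.* The article sets no test or threshold, so such a figure would describe a rule that nobody wrote.
- *That a monitoring committee or interim analysis is required.* Their absence is a defensible choice here.

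The reply does not rescue the indicator. The point rests on what the article states, namely the quantity chosen to stand for unfavourable outcome and the coding of the outcomes.

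**Conclusion.** The concern holds in a limited form. As a between-arm indication of unfavourable outcome, loss to follow-up does not register worsening among clients who complete the interview, about 83% of the sample on the planned figures. No stated outcome supplies a by-arm count of worsening.

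The structural part, that worse-and-reached is scored like unchanged-and-reached, follows from the definitions and needs no assumption. The illustration of 15 extra worsened clients appearing as 0, 5 or 12.5 extra losses rests on an assumed 10-point excess, on 16.7% ordinary loss and on the assumed loss among those clients. That loss may also differ between arms without harm is plausible but unquantified.

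The primary effect estimate is unaffected. What suffers is the trial's ability to say whether some clients did worse. The change is worth making because it is cheap and uses data already planned.

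**What to change.** 1. In *Data security, quality and management*, describe loss to follow-up by arm as a measure of retention and possible selection bias, and remove its role as a stand-in for harm.
2. State that the following will be reported by arm at 6 and at 12 months: increase in AUDIT score; upward shift in AUDIT category; new M.I.N.I. depression or generalised anxiety disorder among clients without it at baseline; and critical events recorded under the interviewer procedure, with date. Give the number interviewed as denominator, with the number lost beside it. AUDIT score is needed as well as category because clients in the top band cannot shift up.
3. If anything is reviewed during the trial, limit it to critical events and marked worsening, defined in advance. The statistician should see it away from interviewers and helpline staff, and outside the monthly meetings, with no efficacy comparison.

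**Cost.** A few sentences of protocol text, a recorded field for critical events if none exists, and one table at each follow-up. No extra visits, interviews or participants are needed. The downside of item 3 is that one person sees by-arm harm counts before the end. The change does not bring the information forward: AUDIT and M.I.N.I. still arrive at 26 and 52 weeks. It makes worsening visible once the interview has been done.

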### Statistical methods

The primary analysis will follow a superiority design applying an intention-to-treat (ITT) approach, i.e., analysing participants based on their random allocation. The alternative hypothesis is that the brief, structured intervention is more effective than usual care in promoting change in a client’s alcohol drinking habits.

#### Statistical analysis

The primary outcome ‘change in AUDIT risk level’ will be analysed as a dichotomous variable where any downward shift (yes/no) from a higher- to a lower-risk level between baseline and follow-up is considered as a clinically meaningful change in drinking habits. The ratio of the cumulative rates of change in the trial groups will constitute the effect measure of the brief, structured intervention versus usual care. General linear models (GLM) will be used to calculate the RR for the outcome event.

Baseline characteristics will be compared between groups in order to detect potential imbalance in predictors of the outcome. If the two groups are not well balanced according to these predictors, multivariable analysis applying logistic regression models will be carried out to estimate odds ratios for the outcome event.

Secondary outcomes (i.e., depression, anxiety, health measures, care seeking) will be analysed using GLM or logistic regression models as described above.

Complementary ‘per-protocol’ and ‘as-treated’ analyses will also be conducted [30]. The ‘per-protocol’ analysis, will only include participants with complete adherence. Complete adherence is defined as: having used the material and received the proactive call (brief, structured intervention); receiving all counselling sessions agreed between the counsellor and the client (usual care). In the ‘as-treated’ analysis, the number of sessions and total duration of the counselling will be considered for each participant, independent of group allocation. These analyses will contribute to the assessment of the effect of the intervention when delivered in standard practice. Possible confounding effects must be carefully monitored in these analyses, since they ignore the random assignment and, therefore, the distribution of baseline risks between participants.

Moderating factors in the analysis include readiness to change, as well as dose-response, i.e., number and length of calls. Further, process data from the records will provide information on the conduct of the proactive calls (adherence).

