### Sample size

The sample size estimation is based on the primary outcome, i.e., decrease in AUDIT risk category, in a superiority design. Based on a previous observational study of the SAH [12], we estimate that 30% in the usual care group will make a downward shift in AUDIT risk level. We estimate that 300 participants will be recruited to the study, of which at least 250 participants will be included in the analytical sample (125 in each experimental group). Based on the analytical sample the study will have more than 90% statistical power to detect a Risk Ratio (RR) equal to or greater than 1.7 for the alternative counselling (i.e., 50% cumulative rate of change in the brief, structured intervention group) as statistically significant at the 5% level. For a RR of 1.3 the power will decrease to about 50%.

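### Covariate adjustment hinges on an undefined baseline imbalance, and the only adjusted result is an odds ratio although the trial is planned and powered on a risk ratio

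*Protocol article*

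**What the plan says.** The protocol article, under Statistical analysis, first fixes the measure: "The ratio of the cumulative rates of change in the trial groups will constitute the effect measure" of the brief intervention against usual care. It then names the model: "General linear models (GLM) will be used to calculate the RR for the outcome event". The abstract also names only the RR.

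The next paragraph adds a conditional step. "Baseline characteristics will be compared between groups in order to detect potential imbalance in predictors of the outcome". The condition follows: "If the two groups are not well balanced according to these predictors". The consequence is that "multivariable analysis applying logistic regression models will be carried out to estimate odds ratios for the outcome event". The paragraph does not list the predictors, say what counts as imbalance, or say how the OR ranks against the RR.

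Secondary outcomes inherit the arrangement: they "will be analysed using GLM or logistic regression models as described above".

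The Sample size section works on the RR alone. For the control arm, "we estimate that 30% in the usual care group will make a downward shift in AUDIT risk level"; the alternative is a "50% cumulative rate of change in the brief, structured intervention group", given there as an RR of 1.7. The Randomisation section states that allocation is simple, so nothing is stratified.

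**The concern.** Two things are fixed badly.

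1. **Adjustment depends on what the baseline table shows.** With simple randomisation and concealed allocation, every baseline difference between the randomised groups is a chance difference. A balance check therefore cannot show whether adjustment is needed. That depends on how strongly a covariate predicts the outcome, which can be judged in advance. Because no criterion is stated, someone must decide at analysis whether the rule has fired and which covariates enter.

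2. **Adjusting also changes the scale.** The adjusted result is an OR, while the declared measure and the design target are RRs. For an outcome expected in 30% to 50% of participants the two are far apart. A reader who compares the adjusted OR with the unadjusted RR, or with the target of 1.7, would be misled. Nothing forces this change, since an RR can be adjusted directly.

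At stake is which covariates stand behind the adjusted estimate and whether it can be set beside the quantity the trial was designed to detect.

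**Working it through.** **Inputs from the protocol.** Usual care 30%; intervention 50% (Sample size); 125 analysed per arm; 5% level (two-sided assumed, as sidedness is not stated). The smaller scenario, RR 1.3, implies 0.30 × 1.3 = 39%.

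**Step 1: reproduce the planned power.** Two-proportion test with pooled variance under the null:
- Mean proportion = (0.30 + 0.50)/2 = 0.40
- Null SE = √(2 × 0.40 × 0.60/125) = 0.0620
- Alternative SE = √((0.30 × 0.70 + 0.50 × 0.50)/125) = 0.0607
- z = (0.20 − 1.96 × 0.0620)/0.0607 = 1.29, so power = 90.2%

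At exactly RR 1.7 (51%) the same formula gives 92.7%. The stated power of more than 90% is reproduced, and it belongs to the RR framing.

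**Step 2: RR and OR at the planned rates.** RR = p2/p1; OR = [p2/(1 − p2)]/[p1/(1 − p1)].

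| Usual care | Intervention | RR | OR |
|---|---|---|---|
| 30% | 50% | 1.67 | (0.50/0.50)/(0.30/0.70) = 2.33 |
| 30% | 51% | 1.70 | (0.51/0.49)/(0.30/0.70) = 2.43 |
| 30% | 39% | 1.30 | (0.39/0.61)/(0.30/0.70) = 1.49 |

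At the design effect the OR is 2.33/1.67 = 1.40 times the RR; in the smaller scenario it is 1.49/1.30 = 1.15 times.

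These are crude ORs. A covariate-adjusted OR moves further away because the OR is not collapsible. For the same 30% versus 50%, with one normally distributed covariate (assumed), it is about 2.45 if the covariate has a log-OR of 0.5 per SD and about 2.77 if it has 1.0 per SD.

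**Step 3: how often chance alone would fire the rule.** The protocol gives no criterion, so this is an assumption with a range. With k independent predictors each tested at level a, the chance is 1 − (1 − a)^k.

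| k | a = 0.05 | a = 0.10 |
|---|---|---|
| 3 | 14% | 27% |
| 5 | 23% | 41% |
| 10 | 40% | 65% |

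**Step 4: does the rule inflate type I error?** 4,000 null trials were simulated with 250 participants, a 30% event rate and five independent covariates, one of them prognostic (log-OR 1.0 per SD). If any covariate differed at p<0.05, the test came from a logistic model adjusted for the unbalanced covariates; otherwise from the unadjusted RR. The rule fired in 22.6% of trials. Type I error was 4.6% with the rule and 4.9% with the unadjusted RR throughout. The simulation error is about √(0.05 × 0.95/4000) = 0.3 percentage points, so no inflation is seen.

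**Step 5: why baseline AUDIT and sex predict the endpoint.** The bands under Primary outcome start at 8, 16 and 20 for men and at 6, 14 and 18 for women. The fall needed to leave the band therefore depends on score and sex:
- Man scoring 15: 8 points; 16: 1 point; 19: 4 points; 20: 1 point; 30: 11 points
- Woman scoring 18: 1 point

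The relation rises and falls in a sawtooth, so a straight-line AUDIT term fits it poorly. As an illustration, assume normal scores with mean 21.2 and SD 6, reliability 0.85, a mean fall of 2 points and 58% men. A linear AUDIT term plus sex then explains about 5% of the outcome variance; a saturated AUDIT-by-sex model explains about 23%.

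**The case against.** The strongest reply is that the protocol fixes the RR without condition and only adds a logistic analysis when imbalance appears. That is a fair reading. A reader might infer that the OR takes over as the headline result, but the text never says the RR is dropped, so a switch cannot be asserted. What stands is that the status of the adjusted result is left open and that it is on a different scale under either reading.

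A reader might also infer that the OR is biased. It is not: it is a different measure, and the protocol labels it as an odds ratio. Exaggeration arises only if it is read as an RR, and it is much milder at RR 1.3 than at the design effect.

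It is tempting, too, to say that the conditional rule inflates false positives. The trigger uses baseline data, not outcomes, and the one rule simulated showed no inflation. The trigger frequencies are hypothetical, since the protocol states neither a test nor a number of predictors.

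The term general linear model could be read as a normal, identity-link model, which would give a risk difference. As the sentence says that the model will yield the RR, a generalised linear model is plainly meant. This is a wording slip.

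Finally, under randomisation the unadjusted RR is valid, and a covariate list may sit in an analysis plan not shown. That answers missing detail. It does not answer a stated rule that ties adjustment to observed balance and to the OR scale.

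**Conclusion.** The point holds as a should-fix. The protocol makes adjustment depend on an undefined judgement of chance imbalance and delivers the adjusted result only as an OR, which cannot be set against the RR the trial is powered on. The gap is 2.33 against 1.67 at the design rates and 1.49 against 1.30 in the smaller scenario. These figures rest only on the protocol's own event rates. The larger adjusted ORs (2.45 to 2.77) depend on assumed covariate strength, and the trigger rates (14% to 40% at p<0.05) on an assumed test and 3 to 10 independent predictors. The documents do not show that the OR replaces the RR, that the estimate is biased, or that type I error is raised.

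**What to change.** - Delete the imbalance trigger. Describe baseline characteristics by group, but do not use them to choose the model.
- Prespecify one primary model that gives an RR: log-binomial, Poisson with robust variance, or logistic regression standardised to a marginal RR.
- Adjust it for sex and baseline AUDIT whatever the observed balance. Enter AUDIT flexibly, for example as baseline risk band plus distance to the sex-specific cut-off, because a linear term may recover little precision.
- Report the unadjusted RR as supportive and any OR as supplementary, labelled as such.
- Apply the same rule to the secondary outcomes.
- Correct general to generalised linear models in the abstract and under Statistical analysis.

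**Cost.** Text changes and slightly more modelling work; no new data, since AUDIT and demographics are collected at baseline and the AUDIT cut-offs already require sex. The suggested form uses five terms beyond the intercept (arm 1, sex 1, band 2, distance 1), against about 125 × 0.30 + 125 × 0.50 = 100 expected events. A log-binomial model may fail to converge, so name one of the other two as the fallback in advance. The article reports recruitment as ongoing, so the change can be made before analysis.
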